### Assignment of Interventions

Participants are assigned to the same group (either control or the treatment group) for 3 consecutive months (interchangeably for 18 months), such that participants recruited in the first 3 months are allocated to the control group and participants recruited in the following 3 months are allocated to the treatment group. This design was chosen to assist participant blinding to group allocation, given the heightened potential for the women recruited to know each other and/or discuss research participation. Since participants in this study are recruited following their first antenatal appointment, participants recruited around the same time will have similar due dates. As membership to parents’ groups and hospital-run parentcraft classes is usually assigned by due date/gestation, and due to the relatively small recruitment pool (Tasmania has a population of 515,000 and only 3 tertiary hospitals), adopting a fully randomized, parallel group controlled design would likely jeopardize participant allocation concealment (ie, differing incentive amounts), thus introducing bias (eg, recruited women declining/delaying enrolment due to allocation, participants not being as motivated to quit smoking due to lesser incentive amount). As well as assigning participants to the same group in 3-month intervals, participants who report knowing another participants or are recruited by another participant are assigned to the same group.

### Interventions

During their initial enrolment visit (visit 1), all participants and their support partners are offered a separate resource pack providing further information and quit references. The content of the packs, selected on the basis of existing resources developed and distributed by not-for-profit organizations and government-funded bodies (eg, Quitline, Cancer Council, and SIDS and Kids), includes informational brochures on the topics of smoking and pregnancy, quitting smoking during pregnancy, a guide for quitting smoking, and smoking and sudden infant death syndrome. A referral and resources summary list (eg, further websites and available mobile phone apps) is also provided that includes telephone numbers of local counseling services. The resource pack specifically designed for partners contains information about the effect of second-hand smoke on children, quit smoking products, and how to be an effective quit buddy. Following the single-blinded, consecutive-month schedule, women are allocated to either the control or treatment group during their enrolment session (Textbox 1).

Control and Treatment group incentives.GroupControlOnly the participant is rewarded with a AUD $50 voucher if they verify as quit during monthly visitsTreatmentBoth participant (1 x AUD $50) and their designated support person (1 x AUD $50) receive a shopping voucher if the participant verifies as quit during monthly visitsIf partner is not present during study visits, participant collects both vouchers

All participants are encouraged to make a quit attempt in the 2 weeks following the enrolment visit in order to promote quit status (verified by less than 7 ppm CO breath sample) and enable incentive issue at the first monthly follow-up, although it is emphasized that each participant is able to decide their own quit timeframe and approach. No other formal smoking cessation counseling support is provided.

All participants are asked to attend 2 further study visits—visit 2 (end-of-pregnancy) and visit 3 (end-of-study)—and have the opportunity to attend monthly visits to verify their non-smoking status and receive incentive voucher/s.

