**Conclusions:**

This study protocol extends the current literature on incentivized smoking cessation interventions for pregnant women by assessing the influence of incentivizing a support partner on short- and long-term abstinence. Key ethical considerations are discussed including potential for receipt (or not) of quit-contingent vouchers impacting negatively on the participant’s relationship with their partner. The findings of the study may have important implications for the role support partners are assigned in smoking cessation programs targeting pregnant women.

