Combining incentives programs with partner support, particularly the co-habiting and/or romantic partner (eg, expectant father) that emphasizes positive support, may therefore be an approach that fosters more effective long-term cessation for pregnant smokers. To our knowledge, only one study to date has explored incentivizing social support to promote smoking cessation in pregnant women. Donatelle and colleagues [23] compared 2 groups: 1 receiving usual antenatal care and 1 which included both the women and their chosen female non-smoking supporter (providing unstandardized, non-formalized, “natural” peer support only) provided with quit-contingent shopping vouchers. Participants in the incentivized partner support group were more likely to be quit at the end-of-pregnancy (32% versus 9%) and at the 2-month postpartum (21% versus 6%) time points compared to usual care. Since this study was not fully factorial (eg, intervention groups consisting of social support only and incentives only, not included), the effect of partner support over and above incentives could not be determined. Furthermore, the support person in the Donatelle et al [23] study was not the pregnant women’s spouse (eg, husband and/or father of child), but rather a female, non-smoking friend, who might arguably have had less vested interest in the health of the expectant child than the expectant father.

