### Eligibility Criteria

Women who express interest in participating in the study (either self-refer or consent to a health professional forwarding their contact details to research staff) are contacted by research staff and screened for eligibility using a previously validated protocol [24]. To be eligible for study entry, women must be (1) pregnant (20 weeks gestation or less); (2) at least 16 years of age; (3) self-report as being a current smoker (“even a single puff in the last 7 days”); (4) attending routine antenatal care provided by the Tasmania Health Service or participating GP center (Tasmanian, Australia); and (5) be able to attend a minimum of 3 appointments at 1 of the 3 data collection sites across Tasmania (Launceston General Hospital, Royal Hobart Hospital, or Mersey Community Hospital). Women younger than 18 years (but 16 years or older) require the consent of their parent, guardian, or senior antenatal health provider to participate in the study.

Potential participants are excluded from study entry if they self-report as non-smoking (ie, “have not smoked, even a single puff in last 7 days”) or if they have a cognitive or intellectual impairment that will inhibit fulfillment of participation requirements (eg, completion of surveys and/or attend organized study appointments). Participants who are found to be “gaming” (eg, those who tell researchers they are pregnant and/or smoking untruthfully to enroll in study) are also excluded from further participation and their data discarded. All participants are asked to nominate and are encouraged to bring along to study visits a support person, preferably a person they co-habit with (eg, spouse, father of child, or family member).

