#### Enrolment Visit

During the enrolment visit (visit 1) participants are asked to complete a battery of questionnaires and provide 2 CO breath samples. Regardless of group allocation, participants are asked to nominate a support person (they are asked to have this person in mind when completing the Partner Interaction Questionnaire), preferably the person they are living with (eg, partner or family member), whose contact details are recorded along with the participant’s own details to assist with future correspondence. While no smoking cessation counseling is provided, participants are offered a resource pack for themselves and their support partner.

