### Planned Analyses

Analyses are planned to test each of the 4 hypotheses.

#### Hypothesis 1

The first hypothesis (H1) is that providing an incentive to both the support partner and expectant smoking mother to quit is more effective than providing an incentive to the pregnant smoker alone at promoting abstinence during pregnancy.

The quit rates of the treatment and control groups will be compared at the end-of-pregnancy time point (visit 2) using chi-square analysis. While no study to our knowledge has compared participant-only incentive with combined participant and support partner incentive, Donatelle et al [23] compared a usual care control group with an incentive plus partner incentive treatment group and found that at the end-of-pregnancy, 32% of treatment group participants had quit (n=105) compared with 9% in the control group (n=102), which indicates a large effect size (*χ*^2^=18.4, N=207, *d*=0.62) [23]. Since the control group in the present study is also receiving incentives, it is anticipated that the effect size may be moderate, rather than large. As such, to determine if there is a significant difference in proportion of women who have quit between control group and treatment group, with the power of .80 to detect an effect size of 0.30, the study will require a total sample size of 108.

#### Hypothesis 2

The second hypothesis (H2) is providing an incentive to both the support partner and expectant smoking mother to quit is more effective than providing an incentive to the pregnant smoker alone at promoting abstinence in the postpartum period.

As per H1 above, treatment and control group abstinence rates will also be compared at the end-of-study (visit 3) and at 12-months postpartum follow-up time points to determine the effect of incentivized partner support on postpartum abstinence. A multi-comparison adjustment will be applied to control for family-wise error.

#### Hypothesis 3

The third hypothesis (H3) is regardless of incentives, women who receive more positive cessation support from their partners (as measured by PIQ-20) are more likely to quit smoking.

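### The treatment arm changes both who is paid and how much is paid, so a positive H1 or H2 supports the package and cannot be uniquely attributed to incentivising the partner

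*Protocol article*

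**What the plan says.** **Arms and amounts.** Trial Design describes two groups. Under Interventions (Textbox 1), a control woman who verifies as quit receives one AUD 50 voucher. In the treatment group the woman and her designated support person each receive one. The textbox adds that if the "partner is not present during study visits, participant collects both vouchers".

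**What both arms share.** All participants nominate a supporter and "are encouraged to bring along to study visits a support person, preferably a person they co-habit with" (Eligibility Criteria). Enrolment Visit repeats the preference: "preferably the person they are living with (eg, partner or family member". The partner resource pack, including its advice on being an effective quit buddy, is offered in both arms (Interventions).

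**What is tested.** H1 is that "providing an incentive to both the support partner and expectant smoking mother to quit is more effective" than an incentive to the woman alone, at end of pregnancy. H2 makes the same contrast postpartum.

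**What is to be concluded.** The Abstract conclusions say the study extends the literature "by assessing the influence of incentivizing a support partner on short- and long-term abstinence". Objectives asks whether partners can be incentivised into more supportive and effective quit buddies. The H2 analysis text describes its comparison as determining the effect of incentivised partner support.

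**What is said about amount.** Assignment of Interventions says full randomisation "would likely jeopardize participant allocation concealment (ie, differing incentive amounts" being the difference at issue). The checks in Sample Size and Checks cover recruitment site and cyclical effects. They do not cover voucher value or who collected it.

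**The concern.** With nomination, encouragement to attend and the partner pack common to both arms, the partner's voucher is the only planned difference. It does two things at once: it makes the partner a named recipient, and it doubles what a verified visit is worth to the pair. When the supporter is absent, both vouchers go into the woman's hands.

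If a larger reward raises quitting by itself, H1 and H2 could both be positive with no change in partner behaviour. The stated implication for the role of support partners in cessation programmes would then rest on an attribution the design cannot make. H1 is the primary hypothesis and H2 carries the long-term claim, so this concerns the trial's main message.

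**Working it through.** **1. Value per verified visit** (Textbox 1; Quit-Contingent Incentive Vouchers and Study Compensation).

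- Control: AUD 50. Treatment: 50 + 50 = AUD 100. Ratio 100/50 = 2.0.
- A woman still smoking at a scheduled visit is offered AUD 10. The pair's gain from quitting at such a visit is therefore 50 - 10 = AUD 40 v 100 - 10 = AUD 90, a ratio of 2.25.

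**2. Why one contrast cannot separate the two factors.** Cross recipient (woman alone, both) with total value (AUD 50, AUD 100):

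| | AUD 50 in total | AUD 100 in total |
|---|---|---|
| Woman alone | control group | not in the trial |
| Woman and supporter | not in the trial | treatment group |

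The difference in quit rates is D = R + A, where R is the effect of naming the partner as recipient (including any interaction) and A is the effect of the extra AUD 50. The data estimate D only. Any split of D between R and A fits equally well, and no analysis plan can change that.

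**3. Who is handed the money.** Let q be the share of the treatment arm's verified visits at which the supporter is absent. The document gives no q, so the whole range is shown. The average value handed to a treatment-arm woman is 50 + 50q, against AUD 50 in control.

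| q | Handed to the woman (AUD) | Pair's total (AUD) |
|---|---|---|
| 0 | 50 | 100 |
| 0.25 | 62.5 | 100 |
| 0.5 | 75 | 100 |
| 0.75 | 87.5 | 100 |
| 1 | 100 | 100 |

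The pair's total is doubled at every q. What varies is how much passes through the woman's hands. The document does not say whether she keeps the second voucher.

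**4. Size up to the primary time point.** Booking-in is usually around 10 weeks and eligibility ends at 20 weeks. The end-of-pregnancy visit is at about 8 months' gestation, taken here as 35 weeks. With 4.35 weeks per month:

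- entry at 20 weeks: (35 - 20)/4.35 = 3.4 months
- entry at 10 weeks: (35 - 10)/4.35 = 5.7 months

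That is roughly 3 to 6 payable months. The maxima are 3 × 50 to 6 × 50 = AUD 150-300 in control, and 3 × 100 to 6 × 100 = AUD 300-600 in treatment.

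**5. Illustration only: how often amount alone would make H1 positive.** Assumptions: 54 per arm (the planned 108 split equally), uncorrected chi-square at two-sided 5% (the article states no alpha), no partner effect, and an assumed gain A from amount alone. Exact binomial enumeration gives the probability of a significant result favouring treatment:

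| A (points) | Control quit rate 20% | Control quit rate 15% to 30% |
|---|---|---|
| 0 | 0.025 | 0.025 |
| 5 | 0.090 | 0.10 to 0.08 |
| 10 | 0.221 | 0.26 to 0.20 |
| 15 | 0.414 | 0.47 to 0.37 |
| 20 | 0.627 | 0.68 to 0.57 |

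This is an ordinary power curve read with A in place of a partner effect. The document supports no particular value of A.

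**The case against.** Much of the case on the other side stands.

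- **The hypotheses match the arms.** H1, the statement of H2, the Abstract objective and the first aim all compare paying both with paying the woman alone. A positive result would make those statements true as worded. This stands, and it confines the problem to attribution.
- **The design is a reasonable trade-off.** It keeps the woman's own named voucher at AUD 50 in both arms. Splitting AUD 50 between two people would equalise the total but halve hers. This stands as a reason for the choice, but it does not supply the missing separation.
- **The gap in the literature is narrowed.** The article says of the earlier incentivised-supporter study that "the effect of partner support over and above incentives could not be determined", because that study had no incentives-only arm. This trial adds one. A reader might infer that it simply repeats the criticised fault. It does not: what is left is a separate confounding with amount.
- **The article does not predict more quitting at AUD 100.** A reader might take "participants not being as motivated to quit smoking due to lesser incentive amount" as such a prediction. The sentence concerns women's reactions if allocation became known under a randomised parallel design. It shows that the amounts were recognised as different, and no more.
- **Textbox 1 does not contradict itself.** A reader might set receive against collects. The text can be read as one voucher designated for each person, with the absent supporter's voucher handed over through the woman.
- **Partner behaviour is measured.** All participants complete the Partner Interaction Questionnaire (PIQ) at each study visit. This can support or weaken a partner explanation. It cannot remove the aliasing, and H3 regroups women regardless of arm.
- **Payments continue to 6 months postpartum.** Totals over that whole period would overstate what bears on H1, so step 4 stops at the end-of-pregnancy visit.

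**Conclusion.** The concern holds as a limit on interpretation. Named recipient and total quit-contingent value are completely aliased (AUD 50 v AUD 100 per verified visit; about AUD 150-300 v 300-600 at most by the end-of-pregnancy visit). H1 and H2 remain valid tests of the package. What the design cannot support is unique attribution of a benefit to incentivising the partner, and three places in the article make or imply it: the Abstract conclusions, the quit-buddy question in Objectives, and the H2 analysis text.

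The aliasing follows from the stated arms and amounts and needs no assumption. The dollar maxima rest on entry at 10 to 20 weeks and a visit at about 35 weeks. The effect of amount on quitting is unknown, so the probabilities in step 5 show sensitivity and do not estimate the actual risk. A stronger reading, that a positive H1 would be a false finding, is not supported, because H1 as worded would still be true of the package.

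This should be put right before results are reported, because it affects what the primary comparison can be said to show. It does not affect the data, the test or the endpoint.

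**What to change.** 1. In the Abstract conclusions, the quit-buddy question in Objectives and the H2 analysis text, describe the contrast as a package: AUD 100 per verified visit, half of it designated for a support person, versus AUD 50 to the woman. State that a positive result will not be attributed to the partner incentive as distinct from the larger total. The wording of H1 and the statement of H2 can stay.
2. Next to the H1 and H2 results, and as far as existing visit and voucher records allow, report for the treatment arm (a) the share of support-person vouchers collected by the woman and (b) the share of women whose supporter never collected one.
3. Report the positive and negative PIQ scores by arm as supportive evidence on whether partner behaviour differed, and say that this does not separate recipient from amount.

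**Cost.** Three changes of wording, one descriptive table and one by-arm summary of scores already collected. No new participants or procedures are needed. Two limits apply. The article does not say that the collector of each voucher was logged, and recruitment has ended, so item 2 may be only partly recoverable. A positive result will also carry a narrower claim.

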### Quit-Contingent Incentive Vouchers and Study Compensation

All participants attending a scheduled visit are provided with some form of voucher compensation. For participants who are still smoking, an AUD $10 voucher is offered. Participants who verify as quit are offered the shopping voucher amount consistent with their group allocation. If a participant is not abstinent at any visit during pregnancy, they are still eligible to receive the quit-contingent incentive at any subsequent visit during pregnancy if they provide a CO reading of less than 7 ppm.

### Verification of Smoking Status

During each visit and telephone call, participants are asked if they have smoked, even a single puff, in the last 7 days. During study visits, participants complete a 14-day timeline follow-back questionnaire as an assessment of self-reported smoking. To verify self-report, all participants are required to provide 2 expired air CO samples using a piCO Simple Smokerlyzer [25]. Expired CO was chosen as the most appropriate biochemical verification method in this study as it is not sensitive to the use of nicotine-containing medication (such as nicotine replacement therapy which may be used by participants), is non-intrusive, immediate (facilitates immediate provision of quit-contingent incentive vouchers), and inexpensive. The CO readings are recorded and if the average of the 2 samples is less than 7 ppm, the participant’s smoking status is recorded as quit and she receives a voucher incentive. A cut-off value of less than 7 ppm was selected based on recommendations from the National Institute of Health and Care Excellence [15], in addition to the precedent set by existing research in the field which accounts for likely second-hand smoke exposure (eg, from support partner) [18,26]. To check whether our results are sensitive to the CO cut-off value, we also repeat our primary analysis using a CO level of less 4 ppm as the cut-off for abstinence. Substantial discrepancies between the results obtained with the 2 cut-off values suggests that participants are “gaming” the system (that is, continuing to smoke but cutting down just enough to receive the abstinence reimbursement). Based on results of previous similar studies [27], we do not expect “gaming” among participants for incentives to be a significant issue.

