### Objectives

The purpose of this study is to determine whether providing incentives to both support person and expectant mother, if she is able to quit smoking, is more effective than providing incentives to expectant mother only, in promoting short- and long-term smoking cessation during pregnancy. In essence, the present study seeks to answer the question: “Can partners (eg, spouse) be incentivized to be more supportive and effective quit buddies to their pregnant smoking partners?”

Specifically, the study aims to determine whether (1) providing an incentive to both the support partner and expectant smoking mother to quit is more effective than providing an incentive to the pregnant smoker alone at promoting abstinence; (2) regardless of incentives, women who receive more positive cessation support from their partners, as measured by the Partner Interactive Questionnaire 20 (PIQ-20), are more likely to quit smoking; and (3) providing incentives for pregnant smokers to quit is more effective than “usual care” antenatal quit smoking services such as brief advice and referral to smoking cessation services (external telephone counseling and smoking cessation nurse) at promoting smoking cessation.

The primary outcome for the study is smoking status (ie, smoking or quit), as determined by self-report 7-day point prevalence, and carbon monoxide (CO) less than 7 particles per million (ppm) at the end-of-pregnancy time point. Secondary outcomes include effect of incentives on long-term (2 months and 12 months postpartum) abstinence and influence of the quality of partner support (positive compared to negative supportive behaviors) on smoking status.

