#### End-of-Pregnancy Visit

Regardless of smoking status, all participants are required to attend an end-of-pregnancy study visit. This second visit occurs at approximately 8 months gestation and participants are asked to provide 2 CO samples and complete a series of questionnaires.

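### The stated rule for recording a woman as quit omits the self-report condition of the primary outcome, and the 4 ppm check is read as gaming although second-hand smoke could give the same result

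*Protocol article*

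**What the plan says.** **Outcome definition.** The Objectives section of the protocol article defines smoking status "as determined by self-report 7-day point prevalence, and carbon monoxide (CO) less than 7 particles per million (ppm) at the end-of-pregnancy time point". Both conditions are required.

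**Recording rule.** Under Verification of Smoking Status, women are asked about smoking in the last 7 days, and CO is introduced as a check on the answer: "To verify self-report, all participants are required to provide 2 expired air CO samples". The rule that assigns the status looks only at the mean of the two readings. When that mean falls under 7 ppm, the woman's "smoking status is recorded as quit and she receives a voucher incentive". It has one condition, the CO mean.

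**Vouchers.** The section on incentive vouchers says that a woman who was not abstinent at one visit can still receive the "quit-contingent incentive at any subsequent visit during pregnancy if they provide a CO reading of less than 7 ppm". The same section also separates women who are still smoking from those who verify as quit, and offers the former a smaller voucher.

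**Who is tested at the primary time point.** "Regardless of smoking status, all participants are required to attend an end-of-pregnancy study visit", and they give two CO samples there. The End-of-Study Visit section says the same of visit 3.

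**Cut-off.** The verification section gives two reasons for 7 ppm: a national guideline recommendation and, in addition, research precedent that "accounts for likely second-hand smoke exposure (eg, from support partner". It repeats the primary analysis at 4 ppm and says of the comparison: "Substantial discrepancies between the results obtained with the 2 cut-off values suggests that participants are" gaming the system, that is, still smoking but cutting down enough to be paid. No other cause is named.

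**The concern.** There are two separate problems.

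First, the article contains two rules for the same status, and they disagree for one group: women who say they have smoked in the last 7 days but whose mean CO is below 7 ppm. Such women can be present at visit 2 (the H1 outcome) and visit 3 (an H2 outcome), because attendance there does not depend on reported abstinence. Counting them as quit raises both quit rates and, if they are equally common among smokers in both arms, narrows the difference between arms.

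Second, the section attaches an interpretation to its 4 ppm analysis that its own reasoning undercuts. If second-hand smoke is a reason for setting the limit at 7 ppm, some abstinent women may read between 4 and 7 ppm. They would count as quit at one cut-off and as smoking at the other without any gaming. A report that followed the sentence as written could draw the wrong conclusion about participants' honesty.

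**Working it through.** No figure in the article is in dispute, so the check is a comparison of sections followed by an illustration with assumed rates.

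**1. The two rules side by side**

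| Woman at visit 2 or 3 | Objectives rule | Verification rule |
|---|---|---|
| Reports abstinence, CO below 7 | Quit | Quit |
| Reports abstinence, CO 7 or more | Smoking | Not recorded as quit |
| Reports smoking, CO 7 or more | Smoking | Not recorded as quit |
| Reports smoking, CO below 7 | Smoking | **Quit** |

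Only the last row differs. The monthly verification visits and the 12-month verification visit are offered only after the woman has reported abstinence by telephone, so that row has little room to occur there. The conflict is confined in practice to visits 2 and 3.

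**2. Effect on the quit rates**

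Inputs: p is the quit rate under the Objectives rule; f is the share of the remaining women who read below 7 ppm. The documents give neither for this trial. Both are assumed, with f equal in the two arms. The planned total of 108 (Hypothesis 1) is taken as 54 per arm.

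Rate under CO alone = p + (1 − p)f, so the difference between arms is multiplied by (1 − f).

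With p = 20% and 33%:

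| f | Control | Treatment | Difference |
|---|---|---|---|
| 0 | 20.0% | 33.0% | 13.0 points |
| 10% | 20 + 80 × 0.10 = 28.0% | 33 + 67 × 0.10 = 39.7% | 13 × 0.90 = 11.7 points |
| 20% | 20 + 80 × 0.20 = 36.0% | 33 + 67 × 0.20 = 46.4% | 13 × 0.80 = 10.4 points |

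At f = 10% this reclassifies 54 × 0.80 × 0.10 = 4.3 women in control and 54 × 0.67 × 0.10 = 3.6 in treatment.

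With the rates of the earlier trial cited under Hypothesis 1 (9% and 32%), power can also be followed. The usual normal approximation for two proportions (pooled variance under the null, unpooled under the alternative), with 54 per arm and two-sided 5% (assumed; the article states no level), gives 0.85 at f = 0, 0.67 at f = 10% (18.1% vs 38.8%) and 0.51 at f = 20% (27.2% vs 45.6%). At f = 0 the two rules agree.

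**3. What the 4 ppm comparison can show**

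Let s be the share of women counted as quit at 7 ppm who read from 4 to below 7 ppm. The rate at 4 ppm is p(1 − s). With s = 20%, 20% becomes 20 × 0.80 = 16% and 33% becomes 33 × 0.80 = 26.4%.

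The formula does not depend on who these women are. If all of them are abstinent and exposed to smoke at home, the rates fall to 16% and 26.4%. If all of them are smokers who have cut down, they fall to the same 16% and 26.4%. The comparison alone cannot tell one cause from the other.

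**The case against.** **The outcome is already defined correctly.** The Objectives section fixes it once, and the verification section introduces CO as a check on self-report. On that reading the disputed sentence is a loosely worded verification step. This largely stands as an account of intent: a joint rule was probably meant, and a reader who inferred a deliberate second, CO-only endpoint would go beyond the text. It does not remove the conflict, because the sentence that assigns the status lacks the condition, and visits 2 and 3 have no self-report gate to supply it.

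**The effect is small and assumed.** This stands. No document gives the share of smokers reading below 7 ppm, and at 10% the difference moves only from 13 to about 12 points.

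**Vouchers do not define the outcome.** Also right. A reader might infer that H1 would be derived from voucher issue; nothing in the article says so. A reader might also infer a bias that differs by arm, because the treatment arm brings a second voucher for a low reading. The documents give nothing from which to judge whether f would differ.

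**The 4 ppm analysis is an ordinary sensitivity check.** Its stated purpose is exactly that, the wording is only suggestive, and gaming is not expected to be a significant issue. All true. It is also tempting to say that 7 ppm exists to allow for second-hand smoke, but the guideline is given first. Nor does any section say what abstinent women living with a smoker actually read. Finally, a reader might link the check to the exclusion and discarding of data for gaming under Eligibility Criteria. The example there is untruthful enrolment, and the verification section excludes nobody on a CO result. What remains is that gaming is the only explanation offered for a discrepancy that has at least one other, named in the same paragraph.

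**Conclusion.** Both points hold in limited form. The article states two rules for quit status that disagree for women who report smoking but read below 7 ppm, and the disagreement bears on visits 2 and 3, hence on H1 and part of H2. Its size is unknown. Under an assumed 10% of smokers reading below 7 ppm in each arm, 20% vs 33% becomes 28% vs 40%: the level of both rates shifts more than the contrast. If no such women occur, the rules give the same result.

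Separately, a substantial discrepancy between the 7 and 4 ppm results does not by itself point to gaming, since second-hand smoke could produce it. This does not show that the 4 ppm analysis is wrong or that 7 ppm is the wrong limit; only the stated inference needs changing.

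**What to change.** **Outcome rule.** In Verification of Smoking Status, state that for the H1 and H2 outcomes a woman is quit only if she reports no smoking in the last 7 days and her mean CO is below 7 ppm, as in Objectives. The wording on voucher eligibility in that section and in the section on incentive vouchers should be reconciled by the investigators; which voucher rule applies is for them to decide.

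**4 ppm analysis.** Keep it, but describe it as a sensitivity analysis that cannot by itself separate gaming from second-hand smoke. Tabulate the shift from 7 to 4 ppm by arm and by partner smoking status. Do not replace the present sentence with a rule that infers gaming only from an arm difference among women without a smoking partner. Women in both arms are paid for a verified quit, so such a rule would miss gaming that is equal in the two arms, and it would miss any among women whose partners smoke.

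**Cost.** One line in the outcome derivation and one extra table. Self-report and CO are taken at the visits, and partner smoking is in the baseline and end-of-study questionnaires, so no new data are needed. The reported quit rates may be slightly lower than under CO alone, and the subgroups in the table will be small with a planned total of 108.
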